In this sense, and based on the results of the aforementioned meta-analysis, non-controllable factors (COVID-19) and the findings of the IAMI trial, we recalculated the VIP-ACS sample size using a statistical Win Ratio (WR) approach, for analysis of efficacy of the double-dose influenza vaccine compared to the standard dose vaccine, in which it was estimated that the inclusion of 1800 patients (900 per group) for a WR of 1.41 with a power of 82.6% and an alpha of 5 %. These data were obtained over 10,000 simulations, considering the following event rates in the control group: death, 7.0%; AMI, 3.4%; stroke, 1.0%; hospitalization for unstable angina, 2.7%; hospitalization for heart failure, 2.9%; emergency revascularization, 1.0% and hospitalization for respiratory infections, 1.0%, and assuming a reduction of these events with double-dose vaccine in: death by 2.0%; AMI by 0.9%; Stroke by 0.3%; Hospitalization for unstable

angina by 0.8%; Hospitalization for heart failure by 0.7%; Emergency coronary revascularization by 0.2% and Hospitalizations for respiratory infections by 0.3%.

Considering that the primary endpoint of the VIP-ACS comprises more individual endpoints than the IAMI trial, and from the meta-analysis studies, the sample size calculation proposed to the VIP-ACS to assess possible reductions in hierarchical events of the primary endpoint is comprehensive and conservative to the purpose of the study, and overcomes the external conditions involved in the COVID-19 pandemic.

The analysis of the primary endpoint will exclude hospitalizations for respiratory causes caused by COVID-19. To this end, a sensitivity analysis and other exploratory analysis of the impact of COVID-19 on VIP-ACS events are planned.

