| II.                                         | Major changes                                         | 
A) Changes in the number of recruited patients and statistical analysis plan.
 
B) Impacts could occur if the original statistical analysis plan was maintained, since the study sample would be sufficient for the previously proposed models.
 
In this sense, with the advent of the COVID-19 pandemic, in which there was a high rate of patients who received influenza vaccine prior to recruitment, and based on the recent results of the IAMI trial, for the study to keep its initial objective with statistical power, the study Executive Committee proposed a hierarchical statistical analysis based on Win Ratio (WR), previously (Sep/Oct. 2021) to the DSMB analyses, in which assuming that the double-dose influenza vaccine reduces Death by 2.0%; AMI by 0.9%; Stroke by 0.3%; Hospitalization for unstable angina by 0.8%; Hospitalization for heart failure by 0.7%; Emergency coronary revascularization by 0.3% and Hospitalizations for respiratory causes by 0.2% will be evaluated with the inclusion of 1800 patients with 82.6% power and 5% alpha. Therefore, it will not be necessary to include 9200 patients, or 953 events related to the primary endpoint, as proposed in version 4.0 of the protocol. The outcome Hospitalization for Respiratory Infections was added to the primary endpoint, since this outcome is a recurrent event in patients with HF after an ACS, and also composed the endpoint (MACE) of studies and analyzes such as: INVESTED and Udell et al; 2013. Analysis of the primary outcome of VIP-ACS will exclude confirmed respiratory events from COVID-19. COVID-19
 |      |

|      |                                  |                                                                                                                                                                                                                                                                                                                                                                                                                                                                 |  |

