|------|----------------------------------|-----------------------------------------------------------------------------------------------------------------------------------------------------------------------------------------------------------------------------------------------------------------------------------------------------------------------------------------------------------------------------------------------------------------------------------------------------------------|--|
|      |                                  | cases will be analyzed in an exploratory manner and by sensitivity tests.                                                                                                                                                                                                                                                                                                                                                                                       |  |
|      |                                  | c) This change occurred prior to the first assessment by the study data and safety assessment committee, in September and October 2021 the hierarchy of endpoints was reassessed, placing hospitalization for respiratory infections last based on aggregated data and assessing the study power with a relative risk reduction of 28%, without any access to interim data by the Executive Committee, only recruitment data and aggregated reported endpoints. |  |
| III. | People in charge for the changes | [name], [name], [name]                                                                                                                                                                                                                                                                                                                                                                                                             |  |
| IV.  | Interim data                     | The only data used for decision making were those referring to the screening and recruitment rate, as well as the rate of aggregated events reported by the investigating sites throughout follow-up, blind to the intervention groups.                                                                                                                                                                                                                         |  |

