| 19                                                                                                                                                                                                                                                                                                             | Data management                  | x |                                                   |                                                                                                                                                                                                                                                                                                                         |    |
| 20                                                                                                                                                                                                                                                                                                             | Statistical methods              |   |                                                   | Evaluation using the Win Ratio (WR) approach for analysis of the double-dose efficacy of influenza vaccine compared to standard dose vaccine will be through the inclusion of 1800 patients (900 per group) to detect a 25% reduction in the primary endpoint relative risk with a power of about 82.6% and a 5% alpha. | 47 |
| 21                                                                                                                                                                                                                                                                                                             | Data monitoring                  | x |                                                   |                                                                                                                                                                                                                                                                                                                         |    |

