patients from an initial sample size of 9000 have been enrolled. This decision was made without any knowledge of data comparing the study groups by the steering committee or by external independent committee. At that time, the sample size was recalculated, changing the analytical method of the primary endpoint from a z-test with first event from a composite outcome to a Win Ratio approach, and including all-cause mortality and hospitalization for respiratory infections (excluding COVID-19) in the primary endpoint. With the participants enrolled at the time and considering the aggregated reported event rates, the study would preserve a power of > 80% for detecting a relative risk reduction of 28% in the components of the primary endpoint, therefore compatible with a recently published randomized trial in the field and a meta-analysis of previous trials suggesting that magnitude of effect as being plausible and clinically relevant. After this decision, the protocol was amended (version 6.0, of 20-Oct-2021) and a new version of the statistical analysis plan was drafted.

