### Expected absolute risk reductions for the components of the primary outcome (representing 28% relative risk reduction)

|                                                                  |      |
|------------------------------------------------------------------|------|
| Death                                                            | 2.0% |
| Myocardial Infarction                                            | 0.9% |
| Stroke                                                           | 0.3% |
| Unstable angina                                                  | 0.8% |
| Hospitalization for heart failure                                | 0.8% |
| Urgent revascularization                                         | 0.2% |
| Hospitalization for respiratory infection
(Excludes COVID-19) | 0.3% |

Sample size and power calculation were based on 10,000 simulations. Based on these aggregated data and assuming independence between events, Bernoulli distribution for event occurrence, exponential distribution of time to outcome, and a 28% relative risk reduction (RRR) with high dose group versus standard dose group, for a two-tailed  $\alpha = 0.05$ , we calculated that the study would have 82.6% power with 1800 patients enrolled (900 per group). This definition of RRR will be a conservative estimate based on a prior meta-analysis suggesting RRR of 48% with the influenza vaccination versus placebo among patients with ACSErro! Fonte de referência não encontrada. and similar to recent IAMI trial a MACE reduction in 28% in ACS patients using influenza vaccine. Of note, although in the IAMI trial the intervention group (in-hospital vaccination after ACS) was compared against placebo, most of the benefit occurred almost

[figure not shown]

immediately, with great separation of event curves within the first 45 days, when the incidence of cardiovascular outcomes is highest. Since we are also comparing the earliness of influenza vaccination, we also expect this magnitude of benefit to be reasonable in our study.

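### Annex B item 20 ties 82.6% power with 1800 patients to a 25% reduction, while SAP 2.3 ties the same power and sample size to 28%

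*Combined protocol and SAP*

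**What the plan says.** Five places in the current documents describe the effect that the 1800-patient design targets.

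- Protocol Annex B, item 20 (statistical methods): 900 per group "to detect a 25% reduction in the primary endpoint relative risk with a power of about 82.6% and a 5% alpha".
- Protocol Annex B, II(b): a list of absolute reductions that "will be evaluated with the inclusion of 1800 patients with 82.6% power and 5% alpha". No single relative reduction is given.
- Protocol Annex B, II(c): the power was reassessed in autumn 2021, "assessing the study power with a relative risk reduction of 28" percent. This sentence gives no power figure.
- Protocol 6.1: the calculation was made "for a WR of 1.41 with a power of 82.6" percent, with control rates and absolute reductions for each component and no single relative reduction.
- SAP 2.1: "the study would preserve a power of > 80% for detecting a relative risk reduction of 28% in the components of the primary endpoint". SAP 2.3 is more specific. It assumes a "28% relative risk reduction (RRR) with high dose group versus standard dose group, for a two-tailed" alpha of 0.05, and on that basis "we calculated that the study would have 82.6% power with 1800 patients enrolled (900 per group".

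Item 20 is not superseded text. The 82.6% is the version 6 figure (version 5 had 81%), and Annex B carries the date of protocol version 6.0.

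**The concern.** One sample size, one alpha and one power cannot belong to both a 25% and a 28% reduction on the same scale. Item 20 therefore claims the design's power for a smaller effect than the SAP says it was calculated for. Annex B is the formal declaration of what changed when the trial went from about 9200 patients to 1800, and item 20 is its statistical-methods entry. Someone relying on it would think the trial misses a true 25% reduction about 17% of the time (100 − 82.6 = 17.4), and might take a null result as firmer evidence against a 25% benefit than it is. The control arm is also vaccinated, so effects smaller than 28% are not far-fetched.

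**Working it through.** **Inputs.** 900 per arm and two-sided 5% (SAP 2.3). Independent components, Bernoulli occurrence and exponential times (SAP 2.3), with 12 months of follow-up and no dropout. Components run in order: death, MI, stroke, unstable angina, heart failure, urgent revascularization, respiratory infection.

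- Control rates: 7.0, 3.4, 1.0, 2.7, 2.9, 1.0, 1.0% in protocol 6.1. SAP 2.3 is the same except 0.6% for revascularization.
- Absolute reductions: 2.0, 0.9, 0.3, 0.8, 0.7, 0.2, 0.3% in protocol 6.1. SAP 2.3 is the same except 0.8% for heart failure.

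**Step 1: win ratio.** For tier k with 12-month risks pC and pT, let λ = −ln(1 − p) and q = 1 − (1 − pC)(1 − pT). Pairs still tied on entering the tier (share T) add T·q·λC/(λC + λT) to wins and T·q·λT/(λC + λT) to losses. Then T is multiplied by 1 − q.

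Death at 28%: pC = 0.07, pT = 0.0504, q = 0.1169, so wins are 0.0682 and losses 0.0486. Summed over the seven tiers with the SAP rates:

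- 28% in each component: 0.1622/0.1160 = 1.398.
- 25% in each component: 0.1618/0.1206 = 1.341.

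The listed absolute reductions give 1.407 (SAP) and 1.388 (protocol). The stated 1.41 therefore fits about 28%, not 25%.

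**Step 2: power.** Power = Φ(ln WR/SE − 1.96). The variance of ln WR at 900 per arm, from simulated two-sample U-statistics, is about 0.0144–0.0152. At the midpoint, SE = √0.0148 = 0.1217.

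- 28%: 0.335/0.1217 − 1.96 = 0.79, power 79%.
- 25%: 0.2935/0.1217 − 1.96 = 0.45, power 67%.

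Simulating whole trials (2,500–4,000 replicates, simulation SE 0.7–0.9 points) agrees. Combined results:

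| Assumed effect | Win ratio | Power |
|---|---|---|
| 28% per component | about 1.40 | 78–80% |
| SAP listed reductions | about 1.41 | about 79% |
| Protocol listed reductions | about 1.39 | 75–78% |
| 25% on the any-event composite | about 1.37 | 72–74% |
| 25% per component | about 1.34 | 67–69% |

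The stated 82.6% is not quite reproduced at 28%. A pooled-score test gives 78–79%, random matched pairs 75–76%, and a one-sided 5% test 85–87%. The SAP's printed z formula applied to all pairs gives nearly 100% power and about 95% type I error, so it is not the source of 82.6%.

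**Step 3: like-for-like drop.** Within the model, 78–79% falls to 67–68%. To anchor on the documents' own power instead, set 1.960 + 0.938 = 2.898 standard errors at 28% and scale by ln WR:

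- Anchored at WR 1.398: 2.898 × 0.2934/0.3350 − 1.96 = 0.58, power 72%.
- Anchored at WR 1.41: 2.898 × 0.2934/0.3436 − 1.96 = 0.51, power 70%.

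Either way the drop is about 10–12 points.

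**Step 4: composite scale.** Under independence the any-event risk is 1 − Π(1 − p). Protocol inputs give 17.64% against 13.07%, a 25.9% reduction. SAP inputs give 17.31% against 12.63%, or 27.0%. A uniform 28% is about 26.5% on this scale. A composite reduction of exactly 25% needs about 26.4% per component: WR about 1.37, power 72–74%.

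**Step 5: both allowances together.** Take the composite reading (ln 1.367 = 0.3126) and also anchor to 82.6%:

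- At WR 1.41: 2.898 × 0.3126/0.3436 − 1.96 = 0.68, power 75%.
- At the protocol inputs' own 1.388: 2.898 × 0.3126/0.3278 − 1.96 = 0.80, power 79%.

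This most favourable combination still falls short of 82.6%.

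**The case against.** The best defence is scale. Item 20 speaks of the primary endpoint, while the SAP's 28% applies to its components. On the any-event composite the protocol's own inputs amount to 25.9%, within a point of item 20, and the like-for-like gap between those inputs (75–78%) and a true 25% composite reduction (72–74%) is only a few points. Loose rounding could account for much of it. This stands in part. It does not clear item 20: neither listed set of reductions gives 25% on that scale, item 20 does not name the scale, and no reading of 25% reaches 82.6%.

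It is also fair that item 20 is a checklist line. The operative sample-size text does not use 25%, nothing in the test or decision rule depends on it, and a null result should be read from the win ratio and its confidence interval.

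Three stronger readings are tempting and unsupported.

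- A reader might set 68% directly against 82.6% and call the true miss rate 32%. The model yielding 68% gives only 78–80% at 28%, so part of that difference is an unexplained offset that has nothing to do with item 20.
- A reader might say Annex B II(c) itself ties 82.6% to 28%. It gives no power figure; the explicit tie is in SAP 2.3.
- A reader might infer that each component was assumed to fall by exactly 28%. The protocol 6.1 inputs imply 20% (0.2/1.0, revascularization) to 30% (0.3/1.0, stroke and respiratory infection).

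**Conclusion.** The inconsistency is real and sits in current text. Item 20 states a design effect of 25% for a calculation that the SAP, and the win ratio in protocol 6.1, place at about 28%. With 900 per arm, the power for a true 25% reduction is about 67–69% per component, 70–72% per component if 28% is anchored to the stated 82.6%, or 72–74% if 25% refers to the any-event composite. The chance of missing it is then about 26–33% (100 − 74 to 100 − 67). Combining the composite reading with the anchoring lowers this to about 21–25%. All of these exceed the 17% item 20 implies.

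The figures assume independent components, exponential times, no dropout, a two-sided 5% test and a valid variance for the unmatched win ratio. They rest on a model that comes within about 3–5 points of the sponsor's 82.6% at 28% but does not match it, so the size of the drop is firmer than any single power figure. This is a misstated design effect, worth correcting; it is not evidence that the sample size or the analysis must change.

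**What to change.** In Annex B item 20, do one of two things.

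- Replace the 25% with the effect used in the calculation and name its scale: win ratio about 1.41, with the listed absolute reductions, which average about 28% across components (5.2/19.0 = 27.4% from the protocol 6.1 inputs, 5.3/18.6 = 28.5% from the SAP 2.3 inputs). Do not write 28% in each component, which would conflict with protocol 6.1.
- Keep 25%, say whether it is per component or on the any-event composite, and report the power obtained by rerunning the sponsor's own simulation at that effect. The approximate figures here should not be inserted in its place.

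Then use the same effect and scale in Annex B, protocol 6.1 and SAP 2.3. The cost is one line in Annex B, matching wording in the other two places and, for the second option, one simulation run. No patients are added. The trial's stated sensitivity to a 25% effect becomes less favourable.

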## SAP SUMMARY OF CHANGES

| Unique SAP version identifier | Date of document version | Sections                                  | Significant changes from previous authorized version                                        |
|-------------------------------|--------------------------|-------------------------------------------|---------------------------------------------------------------------------------------------|
| Version 1.0                   | 18 January 2020          |                                           | N/A - First version                                                                         |
| Version 2.0                   | 14 March 2022            | 1.1 Rationale                             | Addition of results from the IAM trial                                                      |
|                               |                          | 1.2 Objectives                            | Addition of “respiratory complications” to the primary objective of the study               |
|                               |                          | 2.1 Trial design                          | Addition of a paragraph explaining how the trial was modified due to the COVID-19 pandemic. |
|                               |                          | 2.3 Sample size and statistical framework | Change of the primary analysis to the Win Ratio method.                                     |
|                               |                          | 2.4 Interim analysis                      | Clarification that the trial did not have pre-specified stopping rules                      |
|                               |                          | 3.2 Adherence and protocol                | Addition of a paragraph explaining how the patients in the control group                    |

[figure not shown]

|  |  |                          |                                                                                                                                                                                                                                                                                                                                                                                                                      |
|--|--|--------------------------|----------------------------------------------------------------------------------------------------------------------------------------------------------------------------------------------------------------------------------------------------------------------------------------------------------------------------------------------------------------------------------------------------------------------|
|  |  | deviations               | with vaccination received out of the study window due to the COVID-19 pandemic will be handled.                                                                                                                                                                                                                                                                                                                      |
|  |  | 5.1 Outcomes definitions | 
Change of the primary efficacy outcome from a composite of CV death, MI or stroke, to a hierarchical analysis by the Win Ratio method of all-cause death, MI, stroke, unstable angina, hospitalization for heart failure, urgent coronary revascularization and hospitalization for respiratory infection (excluding COVID-19).
 
Addition of hospitalization due to COVID-19 in the secondary outcomes.
 |
|  |  | 5.2 Analysis methods     | 
Change of the primary analysis method from a z-test of proportions to a Win Ratio method.
 
Specification of the Cox proportional hazards model as a secondary analysis of the primary outcome.
                                                                                                                                                                                                          |
|  |  | 5.3 Sensitivity analyses | Addition of a sensitivity analysis including hospitalizations for respiratory infections due to COVID-19 in the primary outcome.                                                                                                                                                                                                                                                                                     |

[figure not shown]

|  |  |                                                           |                                                             |
|--|--|-----------------------------------------------------------|-------------------------------------------------------------|
|  |  | 5.4 Multiplicity adjustments

5.5 Subgroup analyses | These two new section were included in the current version. |
|  |  | 5.6 Additional analyses                                   | An exploratory analysis was added for respiratory outcomes. |

[figure not shown]

[figure not shown]

